**Fig. 1 Fig1:**
[figure not shown]
Consort Flow Diagram for IMPROVE-2 study showing recruitment flow

### Randomisation and allocation concealment

Randomisation will be conducted by an independent off-site statistician based within the Peninsula Clinical Trials Unit using computer generated list of quasi-random numbers. Participants will be randomised with equal probability to the 32 conditions. Randomisation will be stratified according to severity of current depression (moderate PHQ-9 ≥ 10 and < 20 vs. severe PHQ-9 ≥ 20), antidepressant use (receiving a BNF recommended therapeutic dose versus not receiving a recommended dose) and by source of referral (NHS referral vs direct internet referral). All outcome assessors and data analysts will be kept blind to treatment allocation. The therapists will only have contact with the participant during the intervention and will record the outcome data and the nature and level of assistance given to each participant during each module. In order to preserve blinding of the study researcher, randomisation will be conducted by a third party not involved in assessing or treating the participants, who will also inform the therapist, who will be responsible for informing participants of their allocation.

### Sample size calculation

We assumed that the smallest Meaningful Clinical Important Difference (MCID) would be a small effect size (Cohen’s d or standardized mean difference = .2) for the main effect of an individual treatment component or interaction between components on pre-to-post change in depression. Any smaller effect would be of little clinical interest or value. In order to detect a MCID of d = 0.20 with 80 % power at α = 0.10 per treatment component/interaction for pre-post change on depression, we require a sample size of N = 632 (NQuery 7.0). Alpha of 0.1 is recommended for component selection experiments to decrease the relative risk of Type II to Type I error when selecting treatment components; i.e., to avoid prematurely ruling out potentially active treatment components [14, 17]. Conservatively estimating 40 % dropout attrition post-treatment, we require N ≈ 1056 for a traditional ANOVA. However, because there are at least five repeated measures on the primary outcome within the treatment, we can use a latent growth curve model, using mean scores as in ANOVA, which typically requires 30-50 % fewer participants for the same power [44]. Conservatively estimating that the use of growth curve modelling effectively reduces our required sample size by 30 % relative to only using first and last time-point as in ANCOVA, we require N ≈ 736.

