## Methods

### Study design

A single centre, stratified (moderate depression, operationalized as PHQ-9 score < 20; severe depression, operationalized as PHQ-9 score > =20; source of recruitment: directly from the internet versus within an National Health Service Improving Access to Psychological Therapies (IAPT) treatment service; antidepressant use: none versus at a recommended clinical dose), block randomized, single-blind, fractional factorial trial, based in England will be conducted on the internet, randomized at the level of the patient. It will be a full scale internet-delivered component selection experiment with seven experimental factors evaluated, each at two levels ((presence, coded as +1 versus absence, coded as -1 of component; in other words, effect coded), using a 32-condition balanced fractional factorial design (2_IV_
^7-2^)). This design will allow the estimation of all main effects and several pre-specified 2-factor interactions among the seven intervention factors; in statistical terminology, a Resolution IV design because main effects are aliased with 3-way interactions. Table 1 describes the specific combinations of 2-level intervention factors in the experimental design. A full factorial design of seven factors would have required 2^7^ = 128 conditions; the fractional factorial design reduces the total number of conditions by three-quarters.

Within the chosen fractional factorial design, all participants will be randomized to receive at least one component of CBT and in the majority of cases 3 or 4 components of CBT. This design does not have any conditions in which participants receive no treatment components, i.e., there is not a no-treatment, treatment-as-usual, or waiting list control cell, making it suitable for use in a clinical service. Main effects and interactions are estimated based on aggregates across experimental conditions. For each main effect, half of the study population will be randomized to one level of the factor (e.g., conditions 9–16, 25–32 presence of concreteness training) and half will be randomized to the other level of the factor (e.g., conditions 1–8, 17–24 absence of concreteness training); thus, the full sample size can be used to determine each of the main effects (and interactions), making this design efficient for power and sample size.

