### Intervention component factors

The content of the program will be based on CBT for depression, programmed by the research team [https://mindresolve.minddistrict.co.uk] hosted on an established and secure internet-treatment platform provided by MindDistrict, a Dutch internet health services company. All participants will complete a welcome module which includes a mood diary and basic psychoeducation about depression prior to randomisation and then if randomised will receive between 1 to 7 treatment components depending on the randomized treatment condition.

Each module takes around an hour to complete in session and 1-to-2 weeks to practise. Each treatment component will include written psycho-education, images, written vignettes, online experiential exercises using audio-recordings with automatic feedback, downloadable audio exercises to practice skills, interactive questionnaires, video vignettes of patients explaining therapy, and response boxes in which patients write about their experiences and plans. The modules each follow the same basic structure: reflection on previous session; introduction of new technique; practical exercises and planning how to practise or implement the technique in daily life. The intervention is accessed through a secure website, with each participant having a password protected account. Participants’ log-ins will be automatically recorded by the programme, allowing for an automated measure of treatment compliance. Reminder emails will be sent to participants after two weeks if they have not completed the module. The participant can work through each module at his own pace but can only move from one module to the next once the therapist has provided feedback.

All components will involve brief prescribed therapist online support to improve retention and adherence [7], in which secure online written feedback is provided at the end of each completed module, with the option for additional secure messaging between therapist and patient. The coach will highlight any positive steps made and encourage participants to sustain these as well as pointing out areas to focus on over the next module. Participants will also be able to send questions to their assigned therapist throughout the programme if they are having difficulty with a specific exercise. Well-established self-report measures of anxious and depression symptoms (PHQ-9, GAD-7) are presented at the end of each component to assess symptom change.

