### Statistical analysis plan

Data cleaning will follow the protocol set out by Tabachnick and Fidell [59] including range checks for data values. Statistical reporting will follow CONSORT standards [60]. Missing data will be inspected and handled via full information maximum likelihood (FIML) or multiple imputations (MI) as appropriate. Primary analyses will be conducted on the Intention-To-Treat (ITT) sample. A full, detailed analysis plan, including plans for any interim analysis, subgroup analysis, and sensitivity analysis of the primary outcomes, will be prepared and finalised before the analysis.

The primary outcome is change in PHQ-9 score from randomisation baseline to 12 weeks in the intention-to-treat population that involved all patients who were randomly assigned. Secondary outcomes include GAD-7 and process-mechanism measures.

Our analysis will be an Analysis of Covariance (or equivalent regression or growth curve models) for the primary and secondary endpoints. Each main effect will be modelled as a fixed effect, with baseline PHQ-9 as the covariate. Our interest is primarily in tests of ANOVA main effects and interactions. Main effects and interactions are estimated based on aggregates across experimental conditions (see Fig. 1). Models will be fitted using generalized linear mixed models or latent growth curve modelling, equivalent to ANCOVA regression models, adjusted for stratification variables and baseline outcome values.

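### The 30% sample size saving behind N ≈ 736 assumes at least five within-treatment PHQ-9 scores, which 26 of the 32 conditions cannot supply, so the stated 80% power is unsupported

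*Protocol article*

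**What the plan says.** The Sample size calculation section of the protocol article sets its target as follows: "In order to detect a MCID of d = 0.20 with 80 % power at α = 0.10 per treatment component/interaction". The effect is defined "on pre-to-post change in depression", and the result is "we require a sample size of N = 632 (NQuery 7.0"). Allowing for 40% dropout raises this to about 1056.

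The number is then lowered. The reason given is that "because there are at least five repeated measures on the primary outcome within the treatment, we can use a latent growth curve model", supported by a citation for a typical saving of 30–50%. The section takes the lower end, saying that growth curve modelling "effectively reduces our required sample size by 30 % relative to only using first and last time-point as in ANCOVA", and arrives at about 736.

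Three other places bear on this:

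- Intervention component factors gives the timing of the within-treatment scores: "PHQ-9, GAD-7) are presented at the end of each component to assess symptom change". The same section says that participants receive from one to seven components.
- Study design says that participants receive "at least one component of CBT and in the majority of cases 3 or 4 components of CBT".
- Statistical analysis plan says: "Our analysis will be an Analysis of Covariance (or equivalent regression or growth curve models) for the primary and secondary endpoints". Baseline PHQ-9 is the covariate, and fitting is by mixed models or latent growth curves.

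**The concern.** If the PHQ-9 is taken once per component, a participant's number of within-treatment scores equals the number of components allocated. The article itself says that this is usually three or four, so five or more cannot be the general case. Yet the 30% reduction is applied to the whole sample, on top of 40% attrition, and is described as conservative. Participants who leave treatment would also be expected to stop giving end-of-component scores.

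This matters because the design is a component selection experiment. Alpha was relaxed to 0.10 so that active components would not be ruled out too early, and the Discussion intends to discard components that appear inert. If the saving is not realised, the chance of missing a component with d = 0.20 rises from the planned 20% to as much as about 32%, for each of seven components. A reader of a null main effect needs to know the sensitivity the trial really had.

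**Working it through.** **Step 1. Reproduce the stated figures.** Inputs from Sample size calculation: d = 0.20 on change (SD = 1), alpha 0.10, power 80%, 40% dropout, 30% saving. Allocation for each main effect is 1:1 (16 conditions against 16). Sidedness is not stated. Two-sided reproduces the figure; one-sided would give 452.

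- N = 4 × ((1.645 + 0.842) / 0.20)² ≈ 618, or 310 per level and 620 in total after rounding up. The plan's 632 is within 2% of this and has power of about 81%.
- Dropout: 632 / 0.6 ≈ 1053. The plan's 1056 is 33 × 32.
- Saving: 1056 × 0.7 ≈ 739. The plan's 736 is 23 × 32.

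The chain reproduces, so the arithmetic is not at fault. The question is the premise behind the factor 0.7.

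**Step 2. Count the components in Table 1.**

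| Components | Conditions | Number of conditions | Within-treatment PHQ-9 | With baseline and week 12 |
|---|---|---|---|---|
| 1 | 2, 3, 9 | 3 | 1 | 3 |
| 2 | 1, 5, 17, 21 | 4 | 2 | 4 |
| 3 | 6, 7, 12, 13, 18, 19, 25 | 7 | 3 | 5 |
| 4 | 4, 8, 10, 11, 14, 15, 20, 24, 26, 27, 30, 31 | 12 | 4 | 6 |
| 5 | 16, 22, 23, 28, 29 | 5 | 5 | 7 |
| 7 | 32 | 1 | 7 | 9 |

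Five or more within-treatment scores are possible in 5 + 1 = 6 of 32 conditions. The other 26 (81% of participants under equal allocation) have at most four. If baseline and week 12 are added, 3 + 4 = 7 of 32 conditions still have fewer than five. All these counts are before any dropout. The mean number of components is 3.5. For every factor it is 4.0 where the component is present and 3.0 where it is absent, so the number of scores also differs between the two levels being compared.

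**Step 3. Power at N = 736 by the saving actually achieved.** Completers: 736 × 0.6 ≈ 442. With saving s, the effective number is 442 / (1 − s). Power ≈ Φ(0.20 × √(n/4) − 1.645).

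| Saving | Effective n | Power |
|---|---|---|
| 0% | 442 | Φ(2.102 − 1.645) ≈ 68% |
| 10% | 491 | ≈ 72% |
| 20% | 552 | ≈ 76% |
| 30% | 631 | ≈ 81% |

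Without any saving, the effect detectable with 80% power is d = 2 × 2.487 / √442 ≈ 0.24.

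**Step 4. What baseline adjustment would add.** Step 3 is an unadjusted comparison of change between two groups of completers. Let r be the correlation between baseline and week-12 PHQ-9, with equal SDs. The document gives no r; 0.3 to 0.7 is assumed.

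- If d is on the change-score SD, adjustment multiplies the variance by (1 + r)/2. Power on 442 completers is about 83% at r = 0.3, 78% at r = 0.5 and 74% at r = 0.7.
- If d is on the week-12 SD, adjustment multiplies the variance by 1 − r². Power is about 71% at r = 0.3, 78% at r = 0.5 and 90% at r = 0.7.

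**The case against.** The count in Table 1 is hard to dispute. What can be disputed is how much follows from it, and four points deserve weight.

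- **A reader might infer that the planned ANCOVA has only 68% power.** The document does not support that. The analysis section specifies baseline PHQ-9 as a covariate, and across the assumed correlations a true ANCOVA on 442 completers lies above 68% on either scaling. The sample size section invites the confusion by labelling its first-and-last-time-point reference as ANCOVA, but its 632 is the figure for an unadjusted comparison of change. This objection stands.
- **A reader might infer that 80% power is not delivered.** That is not shown either. With d on the change-score SD and r = 0.3, ANCOVA alone reaches about 83%. Other plausible values fall short. The supportable statement is that 80% has not been justified.
- **Growth and mixed models are also allowed.** They can be fitted with fewer than five scores and with unequal numbers per person, and under full information maximum likelihood or multiple imputation the earlier scores of dropouts still count. So the saving need not be zero. This stands as well, but it does not rescue a flat 30% whose stated reason is false for most conditions.
- **Attrition may be below 40%.** Only people who complete the welcome module are randomised, and the 40% is called conservative. At 30% attrition the unadjusted comparison has about 73% power, and at 20% about 78%. That is a reason to show attrition openly in the power statement; it does not support the five-measure premise.

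**Conclusion.** The concern holds in a limited form. The claim of at least five within-treatment measures contradicts Table 1 and the stated timing of the PHQ-9: it fails in 26 of 32 conditions, and in 7 of 32 even when baseline and week 12 are counted. It is the trial-specific reason given for removing about 320 participants (1056 − 736), and the stated 80% power is reached on the protocol's own terms only if the full 30% saving is achieved.

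On those terms power at N = 736 runs from about 68% with no saving to about 81% with 30%. The lower figure assumes 40% attrition, a two-sided test, d on the change score, and no gain from the baseline covariate or from intermediate scores. It is a floor under those conditions, not an estimate of the power of the analysis that will be run. The document gives neither the correlations nor the covariance structure needed to say where between these figures, or above them, the actual analysis lies.

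**What to change.** In Sample size calculation:

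1. Delete the statement that there are at least five repeated measures within treatment, and delete the flat 30% reduction.
2. Keep N = 736 and restate power as a range for d = 0.20 at two-sided alpha 0.10 with 40% attrition. Give about 68% as the floor for an unadjusted completer comparison of change, with 80% power for d of about 0.24 in that case.
3. Give any ANCOVA figure together with the assumed baseline-to-week-12 correlation and the SD on which d is defined; for example, about 74% to 83% for r from 0.7 down to 0.3 on the change-score SD.
4. If a growth-model figure is kept, derive it from the actual Table 1 schedule, with unequal numbers of scores per condition and with attrition from the end-of-component scores, and state the covariance assumptions.

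The cost is a change of wording and a short calculation. The stated power becomes less favourable, or at least less certain. No additional patients are needed and the design is unchanged.

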### Intervention component factors

The content of the program will be based on CBT for depression, programmed by the research team [https://mindresolve.minddistrict.co.uk] hosted on an established and secure internet-treatment platform provided by MindDistrict, a Dutch internet health services company. All participants will complete a welcome module which includes a mood diary and basic psychoeducation about depression prior to randomisation and then if randomised will receive between 1 to 7 treatment components depending on the randomized treatment condition.

Each module takes around an hour to complete in session and 1-to-2 weeks to practise. Each treatment component will include written psycho-education, images, written vignettes, online experiential exercises using audio-recordings with automatic feedback, downloadable audio exercises to practice skills, interactive questionnaires, video vignettes of patients explaining therapy, and response boxes in which patients write about their experiences and plans. The modules each follow the same basic structure: reflection on previous session; introduction of new technique; practical exercises and planning how to practise or implement the technique in daily life. The intervention is accessed through a secure website, with each participant having a password protected account. Participants’ log-ins will be automatically recorded by the programme, allowing for an automated measure of treatment compliance. Reminder emails will be sent to participants after two weeks if they have not completed the module. The participant can work through each module at his own pace but can only move from one module to the next once the therapist has provided feedback.

All components will involve brief prescribed therapist online support to improve retention and adherence [7], in which secure online written feedback is provided at the end of each completed module, with the option for additional secure messaging between therapist and patient. The coach will highlight any positive steps made and encourage participants to sustain these as well as pointing out areas to focus on over the next module. Participants will also be able to send questions to their assigned therapist throughout the programme if they are having difficulty with a specific exercise. Well-established self-report measures of anxious and depression symptoms (PHQ-9, GAD-7) are presented at the end of each component to assess symptom change.

### Functional analysis

Functional analysis (FA) seeks to determine the functions and contexts under which desired and unwanted behaviours do and don’t occur and, thereby, find ways to systematically increase or reduce these behaviours, by exploring their antecedents, consequences, and variability, and then either alter the environment to remove antecedent stimuli that trigger unwanted behaviours and/or practice incompatible and constructive alternative responses to these antecedents. This approach is based on Behavioural Activation (BA) [45, 46] and rumination-focused CBT [29, 47] approaches to depression. Within this module, patients complete questionnaires to identify their warning signs for stress and rumination and to explore the consequences of their behaviour, make plans to alter environmental contingencies that maintain stress, and generate “If Then” implementation intention plans to act differently to those warning signs.

### Relaxation

Within this module, a variant of progressive muscle relaxation and breathing exercises is used to reduce physiological arousal and tension in response to warning signs, based on evidence that this intervention alone reduces depression [30]. The module introduces a rationale for relaxation, provides an online relaxation exercise as a behavioural experiment to test if it reduces tension, and a downloadable relaxation exercise.

### Identifying and challenging negative thoughts

This module follows the standard steps within CBT for depression as outlined in the 1979 Beck manual [28], including psychoeducation about negative automatic thoughts and cognitive distortions, vignettes of identifying and challenging negative thoughts, and written exercises in which patients practise identifying and then challenging negative thoughts using thought records.

### Activity scheduling

This module closely follows the activity scheduling element of CBT for depression [28]. The internet module provides psychoeducation about the negative effects of avoidance, includes questionnaires to help patients identify their own patterns of avoidance, provides guidance on activity scheduling to build up positive activities and reduce avoidance (e.g., breaking plans into smaller steps; specifying when and where to implement activities), and exercises in which participants generate their own activity plans.

### Concreteness training

This module is based on the concreteness training intervention found to reduce symptoms of depression [30] and derived from experimental research indicating the benefits of shifting into a concrete processing style [48, 49]. It provides psycho-education about depression, rumination, and overgeneralization, a behavioural experiment using audio-recorded exercises to compare abstract versus concrete processing styles, and downloadable audio exercises to practise thinking about negative events in a concrete way. In these exercises, patients identify a recent mildly to moderately upsetting difficulty and work through standardized steps: (i) using mental imagery to focus on sensory details during the difficult event, noticing what is specific about the event and the context in which it occurs; (ii) noticing the process and sequence by which the difficult event unfolds (‘How did it happen?’); (iii) focusing on how to move forward by specifying the particular steps and behaviours to do next.

### Absorption training

Absorption training is focused on teaching an individual to mentally engage and become immersed in what she is doing in the present moment to improve her direct connection with experience and enhance contact with positive reinforcers. Within the module, patients complete a behavioural experiment using audio-recorded exercises to compare visualisations of memories of being absorbed versus not being absorbed in a task, learn about flow [50], practice generating a more absorbed mind-set using downloadable audio exercises, and identify absorbing activities.

